### Procedure

Eligible patients willing to participate in the study will be asked to sign informed consent upon which they will be invited by a research assistant to complete the baseline assessment (T0) at their own hospital. Upon completion of T0, the research assistant will use a central web-based randomisation service to randomly allocate a participant to one of the three study arms: (1) GET in addition to UC; (2) CBT in addition to UC; or (3) control group receiving UC (see Fig. 1). Participants assigned to GET or CBT will start the intervention approximately two weeks after T0. Both interventions will be delivered at or near their own hospital over a period of 12 weeks. Participants assigned to CBT will complete a set of additional questionnaires to determine relevant intervention modules prior to the first intervention session. Participants assigned to GET will complete an additional submaximal test to determine physical fitness during the first intervention session. At 14 weeks, participants are invited by the research assistant to complete the post-intervention assessment (T1) at the hospital. Follow-up assessments at 18 weeks (T2) and 26 weeks (T3) are entirely web-based and will be completed at home. For participants that do not have Internet access, a paper version of the follow-up questionnaires will be send to their home address, which can be returned in a self-addressed, pre-stamped envelope.

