### Sample size calculation

Based on the primary outcome measure of the TIRED study, efficacy of one or both interventions is demonstrated when mean fatigue severity (CIS-fatigue) in participants assigned to GET and/or CBT is significantly lower at T1 compared to participants assigned to UC. A clinically relevant difference between the intervention arms and the UC arm of at least 6 points is expected for the primary outcome (CIS-fatigue). Per arm, a minimum number of 51 evaluable participants at T1 would be needed for a *t*-test with a power of 0.80 and a two-sided alpha of 0.025 (corrected to account for the two comparisons: GET versus UC and CBT versus UC). According to Borm et al. [46], using analysis of covariance (ANCOVA) instead of a *t*-test to analyse treatment effects on a continuous outcome measure (CIS-fatigue) increases the power and reduces the needed sample size in RCTs. This proposed ‘design factor’ for ANCOVA can be calculated by multiplying the number of participants needed for the *t*-test by 1 – *p*
^2^, where *p* is the correlation between the outcome measure at T0 and T1. Since no data on the correlation of the CIS-fatigue from earlier trials in this particular patient group were available, we used a conservative approach by assuming a weak correlation (1 – 0.10^2^ = 0.99) and thus the number of participants needed was not reduced. Anticipating an attrition rate of 30%, we aim to recruit a target sample size of 219 participants at T0 (73 participants per arm).

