### Statistical analyses

The statistician who will perform data analyses will be blinded for intervention allocation. To test the efficacy of both interventions compared to UC, an ANCOVA will be performed for each intervention with *fatigue severity* (CIS-fatigue) at T1 as dependent measure, condition as fixed factor and CIS-fatigue screening score as covariate [47]. Missing data is a common problem in palliative care research and is also anticipated in our study as a result of deteriorating health or because the patient has died. Data will be primarily analysed on complete case basis, i.e. only data from evaluable participants with a T1 assessment will be used. The *p*-level is adjusted to 0.025 to account for the two primary analyses, i.e., GET versus UC and CBT versus UC. When statistically significant differences between GET versus UC and/or CBT versus UC are found, additional sensitivity analysis accounting for all randomised participants will be done to explore the impact of missing data. Several methods of imputation are available and the choice will depend on the actual circumstances of missing data. We will record the causes of missing data and careful considerations will be given to which imputation procedure should be used.

In addition, ANCOVA will be performed for the secondary outcomes (*fatigue, quality of life, and functional impairments*), with baseline score (T0) on the dependent measure as covariate. In these exploratory analyses a *p*-level of 0.05 will be used. Longer-term follow-up effects at T2 and T3 will also be tested using ANCOVA, with baseline score (T0) on the dependent measure as covariate. Again, in these explorative analyses a *p*-level of 0.05 will be used. No sensitivity analysis will be done, as the power for follow-up analyses will be limited due to the expected significant amount of attrition.

Mediation analysis will be conducted to explore the possible underlying mechanisms of the expected reduction in fatigue severity (CIS-fatigue) brought on by GET and CBT at T1. Following recommendations of Preacher and Hayes (2008) [48], we will perform multiple mediation analysis using bootstrapping to test the mediating effect of four potential mediators (i.e., changes in *physical activity, physical fitness, self-efficacy with respect to fatigue, and catastrophising in response to fatigue*). We will only perform multiple mediation analysis when there is a significant effect of one or both interventions compared to UC.

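### A complete-case primary analysis at T1, with drop-out expected from illness and death, leaves the primary contrast open to selection bias that the conditional sensitivity analysis does not cover

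*Protocol article*

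**What the plan says.** The Statistical analyses section fixes the primary analysis set: "Data will be primarily analysed on complete case basis, i.e. only data from evaluable participants with a T1 assessment will be used". The model is an ANCOVA of CIS-fatigue at T1 with study arm as factor and the screening CIS-fatigue score as the only covariate.

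Just before this, the section explains why scores will be absent: missing data "is also anticipated in our study as a result of deteriorating health or because the patient has died". The Sample size calculation gives a rate but no cause: "Anticipating an attrition rate of 30%, we aim to recruit a target sample size of 219 participants at T0 (73 participants per arm").

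The plan does include an analysis of all randomised patients. It is a sensitivity analysis, it is done only if GET or CBT differs significantly from UC, and its imputation method is to be chosen in the light of the missing data that occur. Causes of missing data will be recorded.

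Other information will exist on patients without a T1 score. Table 3 lists CIS-fatigue at T0, T2 and T3 and a medical chart review at T1, and the Adherence and treatment integrity section records session attendance. For T1, "participants are invited by the research assistant to complete the post-intervention assessment (T1) at the hospital". By contrast, "Follow-up assessments at 18 weeks (T2) and 26 weeks (T3) are entirely web-based and will be completed at home".

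**The concern.** The reasons the plan gives for missing scores are tied to health, and so plausibly to fatigue. A covariate measured before randomisation cannot carry information on deterioration after it. If drop-out, or the fatigue of those who drop out, differs between arms, the difference among completers is not the difference among the patients assigned to each arm. Yet the Sample size calculation defines efficacy by assigned participants.

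Unequal drop-out is plausible, though no figure in the article supports a particular size. The trial is not blinded, and the arms differ in burden: weekly two-hour exercise sessions, up to ten CBT sessions, or usual care.

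The bias can go either way. It could produce a false claim of benefit, or hide a real one. The planned safeguard operates only in the first case, and by a method not fixed in advance.

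**Working it through.** **1. The plan's own figures.** Inputs from the Sample size calculation: difference 6 points, power 0.80, "two-sided alpha of 0.025 (corrected to account for the two comparisons: GET versus UC and CBT versus UC"), 51 evaluable per arm, attrition 30%.

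- Inflation: 51 / 0.70 = 72.9, rounded up to 73 per arm; 3 × 73 = 219. This matches.
- The SD is not stated. With n = 2 × SD² × (2.241 + 0.842)² / 6², an SD of 9.8 gives 50.7, rounded up to 51. With the noncentral t, an SD of 9.7 gives 51. I use 9.8 below as an assumption.
- Outside the primary contrast: 73 − 51 = 22 per arm, or 0.30 × 219 = 65.7, about 66 in all.

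**2. How much the covariate can repair.** Complete-case ANCOVA is valid if missingness depends only on arm and the screening score. The plan itself assumes a correlation of 0.10 between T0 and T1 scores, deliberately low. On that value a pre-treatment score explains 0.10² = 1% of the T1 variance, so adjusting for one would remove very little selection. A higher true correlation would remove more.

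**3. Size of the bias.** Let p be the missing share in an arm and d the points by which missing patients are more fatigued than observed ones. The completer mean lies p × d below the mean of all patients, so

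bias toward the intervention = pI × dI − pU × dU

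(I = intervention, U = UC). All values of p and d are assumptions. The type I error is for the completer comparison under no true effect, SD 9.8, 73 randomised per arm, nominal 0.025, without covariate adjustment.

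| Missing, I vs U | d (both arms) | Bias (points) | Type I error |
|---|---|---|---|
| 30% vs 30% | 3, 6 or 10 | 0 | 0.025 |
| 35% vs 25% | 3 | 0.3 | 0.027 |
| 35% vs 25% | 6 | 0.35×6 − 0.25×6 = 0.6 | 0.032 |
| 35% vs 25% | 10 | 1.0 | 0.045 |
| 40% vs 20% | 3 | 0.6 | 0.032 |
| 40% vs 20% | 6 | 0.40×6 − 0.20×6 = 1.2 | 0.054 |
| 40% vs 20% | 10 | 2.0 | 0.112 |

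Equal drop-out does not guarantee zero bias: with 30% missing in both arms, dI = 8 and dU = 4, it is 0.30×8 − 0.30×4 = 1.2 points. What matters is whether p × d is equal across arms.

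**4. The opposite direction.** Suppose UC loses 40%, the intervention arm 20%, and d = 6. A true 6-point benefit appears as 6 − 1.2 = 4.8 points. The standard error is 9.8 × √(1/58.4 + 1/43.8) = 1.96, and 4.8 / 1.96 = 2.45 against a critical value of 2.24, so power is about 0.58. In the remaining 42% or so of such trials the result is not significant and the all-randomised analysis is not run.

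**5. Deaths.** A patient who died before T1 has no T1 fatigue, so d has no meaning for that patient. The formula applies to patients alive at T1 with a missing score. The more of the 30% that is due to death, the smaller p becomes and the more the question is one of definition. The article gives no split.

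**6. Would a repeated-measures model suffice?** T1 is the first assessment after baseline. For a patient who leaves before T1 and does not return there is no post-baseline score, so that patient adds nothing to the T1 contrast, and under monotone drop-out the model gives essentially the complete-case answer. T2 and T3 scores help only for patients who miss T1 and come back.

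**The case against.** The plan is coherent on its own terms. It sizes the trial on patients evaluable at T1 ("Per arm, a minimum number of 51 evaluable participants at T1 would be needed for a" *t*-test), analyses that same set, and the sample size reproduces. It also foresees missing data, records the reasons, and plans an analysis of all randomised patients. Bias is a risk and not a certainty, and the bias figures rest wholly on assumed p and d. The middle scenarios give 0.6 to 1.2 points; the type I error of 0.112 needs both a 40% versus 20% imbalance and a 10-point excess. All of this stands, and it limits the claim.

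A reader might infer four stronger things, none of which the article supports:

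- *That 30% will be lost to deterioration and death.* The rate and the causes stand in different sections and are never joined.
- *That data on patients without T1 are ignored altogether.* That is true of the primary test only.
- *That patients too ill for the hospital visit at T1 will generally supply scores later.* The home format of T2 and T3 makes this possible, but no figure is given and the plan expects substantial attrition at follow-up. Nor does the article say that home completion of T1 is refused; a fallback may stand in the full protocol.
- *That a mixed model over T1 to T3 would cure the problem.* Step 6 of the working shows why it would not.

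The planned sensitivity analysis does not answer the concern. Making it conditional on significance leaves a null result produced by selection unexamined, and leaving the method open weakens its value as a check on a positive result.

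**Conclusion.** The concern holds as a risk built into a stated rule, not as an arithmetic error or a demonstrated bias. The primary test conditions on having a T1 score, while the plan expects scores to be lost for health reasons and adjusts only for a pre-randomisation score. About 66 of 219 patients would be outside it.

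With missing patients 6 points worse and losses of 35% versus 25% or 40% versus 20%, the bias is 0.6 or 1.2 points, that is 10% or 20% of the 6-point target. The type I error becomes 0.032 or 0.054 instead of 0.025. These sizes rest on assumed missing shares, an assumed excess fatigue, an SD of 9.8 back-solved from the sample size, and all missing patients being alive at T1. If missing share times excess fatigue is equal across arms, the bias is zero.

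The firmest part does not depend on those assumptions: the only planned analysis of all randomised patients is triggered by significance and has no prespecified method.

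**What to change.** - Make the primary T1 analysis a prespecified multiple imputation, by arm, for randomised patients alive at T1. Keep the ANCOVA and the 0.025 level for each comparison. Use as auxiliary variables T0 CIS-fatigue, T2 and T3 CIS-fatigue where available, T1 chart data, and sessions attended (GET and CBT arms only, since UC has no study sessions).
- State how deaths before T1 enter the estimand, and report deaths by arm beside the primary result.
- Keep the complete-case ANCOVA as a supportive analysis.
- Prespecify the missing-data sensitivity analyses, including departures from missing at random that may differ by arm, and run them whatever the primary result.

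The cost is changed wording and modest extra programming, with no new data collection. The primary result would rest on scores being missing at random given the auxiliary data. That uses more of what is known about each patient than the complete-case assumption does, but it remains untestable, which is why the departures from it must be examined. If few missing patients return at T2 or T3, most of the gain has to come from chart and attendance data, and it may be limited.

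### The fixed 0.025 split for the two primary comparisons is valid, but Holm's step-down on the same two tests would give more power for a second success at the same 5% familywise error

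*Protocol article*

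**What the plan says.** The Sample size calculation section of the protocol article counts efficacy as shown if either intervention, or both, gives significantly lower CIS-fatigue than usual care at T1. GET versus UC and CBT versus UC are therefore two separate claims.

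- **Planned difference:** "A clinically relevant difference between the intervention arms and the UC arm of at least 6 points is expected".
- **Sample size:** "a minimum number of 51 evaluable participants at T1 would be needed". The calculation assumes a t-test at 80% power, and its two-sided level of 0.025 is described as "corrected to account for the two comparisons: GET versus UC and CBT versus UC".
- **Covariate gain:** a design factor of 0.99 was considered, and "thus the number of participants needed was not reduced".
- **Attrition:** 30%, giving 73 per arm and 219 in total.
- **Analysis:** the Statistical analyses section repeats the rule. The p-level "is adjusted to 0.025 to account for the two primary analyses, i.e., GET versus UC and CBT versus UC".

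No step-down or alpha-recycling rule appears in the article, and no SD for CIS-fatigue is given.

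**The concern.** Under the stated rule each comparison faces 0.025 whatever the other one shows. Holm's procedure orders the two p-values, tests the smaller at 0.025 and, only if that is significant, tests the larger at 0.05. It rejects everything the stated rule rejects and sometimes more. It keeps the familywise error at or below 5% whatever the correlation between the tests, and it needs no ordering of the arms and no further assumption.

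At stake is the second claim. Suppose one intervention is significant at 0.025 and the other gives a p-value between 0.025 and 0.05. The plan cannot then claim efficacy for the second, although 5% familywise control does not require that restriction. Recruitment is described as difficult and 30% attrition is expected, so power that needs no more patients is worth having.

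**Working it through.** **Inputs.** From the protocol article: 51 evaluable per arm, a difference of 6 points, power 0.80, two-sided alpha 0.025 per comparison, 30% attrition, and equal numbers per arm. With equal arms and a shared UC arm, the two test statistics have correlation 0.5. Assumption: the SD, which is not stated.

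**1. The plan's own figures.** 0.05/2 = 0.025. 51/(1 − 0.30) = 72.9, rounded up to 73, and 3 × 73 = 219. Both agree with the plan.

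**2. The implied SD.** For a t-test with n per arm, the noncentrality is δ/(SD × √(2/n)) on 2n − 2 degrees of freedom. With n = 51 and δ = 6, the two-sided 0.025 critical value on 100 df is 2.276. Power of exactly 0.80 needs a noncentrality of about 3.122, so SD = 6/(3.122 × √(2/51)) ≈ 9.70. SDs from about 9.61 to 9.70 lead to n = 51 by the t-test, and about 9.73 to 9.83 by the normal approximation. I use 9.70 and show a range.

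**3. Comparison of the two rules.** Simulation of three arms of 51 with a shared UC arm and pairwise t-tests, 2,000,000 replicates per scenario, SD 9.70:

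| True effects (points) | Quantity | 0.025 each | Holm |
|---|---|---|---|
| 6 and 6 | each comparison | 80.0% | 84.7% |
| 6 and 6 | both | 68.8% | 78.1% |
| 6 and 6 | at least one | 91.3% | 91.3% |
| 6 and 3 | weaker arm | 24.2% | 33.0% |
| 6 and 3 | stronger arm | 80.0% | 80.6% |
| 6 and 0 | effective arm | 80.0% | 80.1% |
| 6 and 0 | false claim, ineffective arm | 2.5% | 4.3% |
| 0 and 0 | any false claim | 4.65% | 4.65% |

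Check by arithmetic for 6 and 6, using P(both) = 2 × P(each) − P(at least one). Single-step: 2 × 80.0 − 91.3 = 68.7. Holm: 2 × 84.7 − 91.3 = 78.1. Both agree with the table to rounding.

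**4. Sensitivity to the assumed SD** (effects 6 and 6, power for both):

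| SD | 0.025 each | Holm |
|---|---|---|
| 9 | 77% | 85% |
| 9.7 | 69% | 78% |
| 10 | 65% | 75% |
| 11 | 54% | 65% |

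The level moves with the SD. The gain stays at about 8 to 11 percentage points, and its direction does not depend on the SD.

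**5. Error when one arm works.** With a true effect of 10 points in one arm and none in the other, the first test almost always succeeds. The ineffective arm is then in effect tested at 0.05, and its false-claim rate under Holm is 5.0%. That is the ceiling.

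**The case against.** The strongest reply is that nothing here is wrong. One rule is stated, it controls the familywise error, and the sample size and the analysis both use it. Each comparison has its planned 80% power. All of that stands. A reader might infer that the multiplicity plan is invalid or the trial underpowered; the article supports neither.

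A reader might also infer that the change is free. It is not:

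- **Per-claim protection.** The stated rule holds the false-claim rate for each intervention at 2.5% even when the other one works. Holm lets it rise to about 4.3% if the other effect is 6 points, and to 5% at most. For two separate claims, preferring the tighter protection is a defensible choice.
- **Intervals.** 97.5% intervals always agree with decisions at 0.025. Under Holm a second comparison can be declared significant while its 97.5% interval includes zero.
- **Timing.** Recruitment is ongoing in a non-blinded trial, so relaxing the primary success rule needs an amendment and a clear record of when it was made.

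The gain is also narrow. It is nil for showing at least one effect, and almost nil if only one intervention works.

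Finally, it is tempting to say that the plan forces the second intervention to be called ineffective. The article says when efficacy is demonstrated. It does not say that a non-significant result shows absence of effect, and a p-value of 0.03 could still be reported with its estimate and interval.

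**Conclusion.** The point holds as an available gain in efficiency, not as an error. On the same two tests and the same patients, Holm is never less powerful than the stated rule and keeps familywise error at or below 5%. If both interventions reach the planned 6 points, it adds about 5 percentage points of power per comparison (80.0% to 84.7%) and about 9 for showing both (68.8% to 78.1%).

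That scenario is relevant, because the article expects at least 6 points for the intervention arms and treats them as separate claims. The power levels rest on an SD of about 9.7, back-solved from the stated 51 per arm, on t-tests without covariate gain, and on 51 evaluable participants in every arm. This is a cheap improvement worth making; the trial's validity does not depend on it.

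**What to change.** Replace the fixed level in the Statistical analyses section with one sentence: *The two primary p-values are tested by Holm's procedure at two-sided familywise alpha 0.05 (smaller p at 0.025; if significant, larger p at 0.05).*

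Keep the sample size at 0.025 as a conservative basis, so 51 evaluable per arm and the target of 219 do not change. Continue to report 97.5% intervals, and state in advance that such an interval may include zero for a second comparison declared significant at 0.05.

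Make the change by dated amendment while the analysing statistician is still blinded to allocation. It costs the amendment itself, the possible mismatch between interval and decision, and the higher false-claim rate for an ineffective arm when the other arm works. It needs no more patients, data or analyses. If the team prefers 2.5% protection for each claim, keeping the present rule and saying so is also acceptable.

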### Randomisation

A central web-based randomisation service provided by an independent statistician will be used. Randomisation will be stratified by centre. We will use block randomisation to reach the same number of participants in all study arms. The ordering of blocks and their respective size will be unknown for the research assistants and coordinating researcher. When possible, minimisation on gender will be performed in order to balance the gender distribution in all study arms. If block randomisation restricts the choice to two or only one study arm, minimisation will always be overruled by block randomisation. A research assistant will perform allocation upon completion of T0 in the presence of the participant.

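### The all-randomised sensitivity analysis for the complete-case primary outcome is promised only if a comparison is significant, so a null result carries no commitment to examine missing data

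*Protocol article*

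**What the plan says.** All of the following is in the protocol article.

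- **Primary analysis.** Statistical analyses plans an ANCOVA of CIS-fatigue at T1 for each intervention against UC, on complete cases: "only data from evaluable participants with a T1 assessment will be used". Missing data are expected because patients deteriorate or die.
- **Sensitivity analysis.** The trigger is a statistically significant difference for GET versus UC "and/or CBT versus UC are found, additional sensitivity analysis accounting for all randomised participants will be done". Its stated aim is to explore what the missing data do to the result.
- **Method.** Several imputation methods are said to be available, and "the choice will depend on the actual circumstances of missing data". Causes of missing data will be recorded and the procedure chosen with care. The analysing statistician is blinded to allocation.
- **Amount of missing data.** Sample size calculation: "Anticipating an attrition rate of 30"%, not broken down by arm or by cause.
- **Other use of the dropout reasons.** The section on refusal and study dropout analyses them for generalisability, not for bias in the treatment comparison.

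**The concern.** The effect of missing data on an estimate does not depend on whether its p-value falls below 0.025. Patients who are too ill to attend T1 are likely to be more fatigued than those who attend. If they are lost unevenly across arms, or if they differ from completers by different amounts in different arms, the complete-case difference is biased, and the bias can go either way. Uneven loss is plausible here: the trial is unblinded, and intervention participants have regular therapist contact that UC participants do not.

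The plan guards one side only. A significant result will be tested against the missing data. A result that is null for both comparisons will not, unless someone decides to do so outside the stated plan. A conclusion that neither intervention reduces fatigue could then rest solely on participants well enough to complete T1, in a trial that expects to lose nearly a third of its sample.

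**Working it through.** **1. The plan's own figure.** Inputs from Sample size calculation: "a minimum number of 51 evaluable participants at T1 would be needed" per arm, 30% attrition. 51 / (1 − 0.30) = 72.9, so 73 per arm and 3 × 73 = 219, as stated. Expected missing at T1: 0.30 × 73 ≈ 22 per arm, 0.30 × 219 ≈ 66 in all.

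**2. Implied SD.** No SD is given. The other inputs are a difference "of at least 6 points is expected for the primary outcome (CIS-fatigue"), a t-test "with a power of 0.80 and a two-sided alpha of 0.025", and equal arms (Randomisation). Solving the non-central t power for n = 51 per arm gives SD ≈ 9.70. Then SE = 9.70 × √(2/51) ≈ 1.92, and the smallest significant difference is t(0.9875; 100 df) × SE ≈ 4.4 points.

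**3. When both comparisons escape or meet the trigger.**

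| GET vs UC | CBT vs UC | All-randomised analysis promised? |
|---|---|---|
| significant | significant | yes, both |
| significant | null (or the reverse) | yes for the significant one; unclear for the null one |
| null | null | no |

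By the plan's own power, a comparison with a true 6-point effect is null 20% of the time even without dropout bias.

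**4. Illustration A: unequal missingness.** Let δ be the mean fatigue of missing minus observed participants, the same in each arm, and π the missing proportion. An arm's full mean is its observed mean + πδ, so the complete-case difference (UC minus intervention) is too small by δ × (π_UC − π_int). The ranges for δ and the π difference are assumptions. Power is held at n = 51 per arm.

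| δ | π difference | Bias | Power at 6 − bias | Rejection if no true effect and bias favours the intervention |
|---|---|---|---|---|
| any | 0 | 0 | 0.80 | 0.025 |
| 4 | 0.10 | 0.4 | 0.738 | 0.028 |
| 8 | 0.20 | 1.6 | 0.508 | 0.079 |

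**5. Illustration B: equal 30% missingness, unequal gap.** If δ is g points larger in UC than in the intervention arm, the complete-case difference is 6 − 0.3g. Again g is an assumption.

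| g | Complete-case difference | Probability not significant |
|---|---|---|
| 0 | 6.0 | 0.20 |
| 2 | 5.4 | 0.30 |
| 4 | 4.8 | 0.41 |
| 6 | 4.2 | 0.53 |

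The difference falls below 4.4 once g exceeds about (6 − 4.37) / 0.3 ≈ 5.4 points. A gap of opposite sign would inflate the effect instead.

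Both illustrations apply to missing participants who are alive at T1; a missing fatigue score has no clear meaning for someone who has died.

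**The case against.** The strongest reply is that the primary test, its alpha and the sample size are untouched, that a sensitivity analysis does not change the primary decision, and that the plan checks robustness where efficacy would be claimed. That stands, and it is why this is not a must-fix. It does not answer the asymmetry.

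Four stronger readings are tempting, and the text does not support them.

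- *The plan forbids the check after a null result.* It promises the analysis when significance is found and is silent otherwise. Where the authors want none, in the following paragraph on secondary and follow-up analyses, they say so.
- *A null comparison is never examined.* The and/or wording may cover both comparisons once one is significant. Only the doubly null case is clearly without a commitment.
- *The imputation method is chosen after the p-value is known.* The section ties the choice to the pattern and causes of missing data and gives no timing. The statistician is blinded to allocation, and an analysis plan that is not shown could fix the method beforehand. Leaving the exact imputation model to such a plan is normal.
- *Fatigue scores will be imputed for patients who died.* Death is named as a cause of missing data, but its handling is not stated. The number of deaths by T1 is also unknown: entry requires a treatment plan based on expected survival of at least 6 months, and T1 is at 14 weeks.

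It is also fair to say that the document gives no gap, no difference in missingness between arms and no SD, so the calculations cannot show that bias will occur, or in which direction.

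**Conclusion.** The concern holds in a limited form. The condition on significance is written into the plan, and following it leaves a doubly null primary result without any committed examination of missing data, with about 66 of 219 participants expected to be absent from the analysis. When one comparison is significant, coverage of the other is ambiguous.

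The size of the potential distortion can only be illustrated. Under the assumed gaps and the back-solved SD of 9.70, it runs from none to 1.6 points in illustration A, and to 1.8 points at g = 6 in illustration B, against a 6-point target. The direction is unknown, which is itself the reason why the check should not depend on the result. Severity: should-fix.

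**What to change.** In Statistical analyses, delete the significance condition and state that the all-randomised sensitivity analysis will be run for both comparisons whatever the primary result. Fix the method before comparative results are known; multiple imputation under missing at random, with a delta-adjusted tipping-point version, is one suitable choice. Report deaths before T1 separately from other missing T1 values, by arm, and do not impute them in the same way.

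A rank-based analysis with death as the worst outcome is optional. It targets a different estimand from the planned mean difference and is not needed to correct this point.

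Cost: a changed sentence and a few more analysis runs. Causes of missing assessments are already to be recorded, so no new data are needed, and N stays at 219.
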